#### Secondary analyses

##### Cost effectiveness

The quality of life measures (i.e. QLQ-C30; QLQ-LC13) will be used to calculate Quality of Adjusted Life Years (QALYs) for each individual. Costs and effects (in terms of QALYs) will be combined in the incremental cost-effectiveness ratio (ICER). The ICER expresses cost-effectiveness in terms of incremental costs per QALY gained. To estimate confidence intervals for the mean of the ICER a non-parametric bootstrapping method will be used, performing 1000 replications of the original data. In order to express the implications of the cost-effectiveness results more clearly, a cost-acceptability curve will be constructed. In case of dominance, a full cost analysis will be conducted to estimate the mean savings per patient per year.

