#### Baseline

Patients and partners are interviewed to obtain demographics and clinical characteristics, after which they are screened for cognitive impairments with the MMSE [33]. After that, baseline questionnaires, including the Distress Thermometer (DT) [34,35], are administered, followed by randomization. Table 1 shows the assessment instruments and time points at which the questionnaires are administered to patients and partners.

**Table 1 T1:** Measurements and corresponding time points for patient and partner

**Measure**	**Target**	**T0**		**T1**		**T2**	
		**pt**	**pr**	**pt**	**pr**	**pt**	**pr**
MMSE	Cognitive impairments	x	x				
DT	General distress	x	x				
HADS	Psychological distress	x	x	x	x	x	x
QLQ-C30	Quality of life	x		x		x	
QLQ-LC13	Quality of life	x		x		x	
SIP	Impact of sickness	x		x		x	
SPPIC	Caregiver burden		x		x		x
CRA-SE	Caregiver self-esteem		x		x		x
IMS-S	Relationship satisfaction	x	x	x	x	x	x
MIS	Communication about cancer	x	x	x	x	x	x
SAIL	Spirituality	x	x	x	x	x	x
FFMQ	Mindfulness skills	x	x	x	x	x	x
SCS	Self-compassion	x	x	x	x	x	x
RRS-EXT	Rumination	x	x	x	x	x	x
IES	Psychological stress reaction	x	x	x	x	x	x
Diary	Health care use, work absence	Monthly during study period for pt					
Calendar	Mindfulness adherence	Monthly during study period for pt and pr					

*Note.* T0 = Baseline measurement; T1 = Post-intervention measurement; T2= 3-month follow-up measurement; pt = Patient; pr = Partner; MMSE = Mini Mental State Examination; DT = Distress Thermometer; HADS = Hospital Anxiety and Depression Scale; QLQ-C30 = Quality of Life – Cancer; QLQ-LC13 = Quality of Life – Lung Cancer; SIP = Sickness Impact Profile; SPPIC = Self-Perceived Pressure from Informal Care; CRA-SE = Caregiver Reaction Assessment – Care-Derived Self-Esteem; IMS-S = Investment Model Scale-Satisfaction; MIS = Mutuality and Interpersonal Sensitivity; SAIL = Spiritual Attitude and Involvement List; FFMQ = Five Facet Mindfulness Questionnaire; SCS = Self-Compassion Scale; RRS-EXT = Rumination Response Scale – Extended Version; IES = Impact of Event Scale.

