#### Randomization

Randomization is stratified according to setting and minimized for (a) stage of disease (curative *versus* palliative), (b) baseline level of anxiety and depressive symptoms (anxiety or depression subscale score of Hospital Anxiety and Depression Scale (HADS) <8 *versus* ≥8), (c) treatment during MBSR (no treatment *versus* chemo- and/or radiotherapy) and (d) participation (patient alone *versus* partner alone *versus* patient and partner together). Randomization is computerized, using a randomization website, specifically designed for this study, on which the researcher can fill out the required data. The researcher communicates treatment allocation to the nurse practitioner, who informs the patient and/or partner.

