### Intervention

The MBSR curriculum used is primarily based on the Mindfulness-Based Stress Reduction programme as developed by Kabat-Zinn [28] but contains some elements of the MBCT programme by Segal, Williams and Teasdale [29], like psycho-education on the interrelatedness of feelings and thoughts. Moreover, some modifications have been made to make the intervention more suitable for patients with lung cancer and their partners, such as psycho-education about grief [36]. In addition, a mindful communication exercise in which partners talk with each other about the cancer was added. The programme consists of 8 weekly 2.5-hour sessions, a silent day between session six and seven and home practice assignments of about 45 minutes, 6 days per week. Participants receive a set of CDs with guided mindfulness meditation exercises for home practice and a folder with information and home practice instructions for the forthcoming week. Table 2 shows the content of the MBSR programme per session. The MBSR courses are taught by mindfulness teachers with extensive training in MBSR. They all fulfil the advanced criteria of the Center for Mindfulness of the University of Massachusetts Medical School [37] and maintain a regular personal meditation practice. Teachers were trained, supervised and assessed to ensure their competency levels met the qualification criteria to instruct the MBSR classes. During the trial, teachers will receive weekly supervision and a number of sessions will be videotaped to evaluate competence and adherence with the Mindfulness-Based Interventions – Teaching Assessment Criteria [38].

**Table 2 T2:** Content of MBSR programme per session

**Theme of session**	**Meditation exercise**	**Didactic teaching**	**Homework**
1. Automatic pilot	- Bodyscan	- Intention of participating	- Bodyscan
		- Raisin exercise	- Eating one meal mindfully
			- Attention for routine activity
2. Mindfulness of the breath	- Bodyscan	- Imagery exercise to demonstrate relationship between thoughtsand feelings	- Bodyscan
	- Sitting mediation with focus on breath		- Attention for breath
			- Awareness of pleasant events
			- Attention for routine activity
3. Observing limits	- Yoga while lying down	- Seeing exercise to demonstrate difference between observation and interpretation	- Bodyscan or yoga
	- 3-min breathing space		- Sitting meditation
			- Awareness of unpleasant events
			- 3-min breathing space

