#### Primary analyses

The samples of lung cancer patients and partners will be analyzed separately. Baseline characteristics of the population will be compared between MBSR and control group to ensure that key variables were evenly distributed by randomization. First, analyses will be based on the intention-to-treat approach. Next, we will perform per-protocol analyses with the treatment-adherent sample (i.e. in the MBSR condition participants have to attend at least four of the eight MBSR sessions [73] and in the TAU condition participants do not attend a mindfulness-based programme).

We will use linear mixed models to analyze all outcome variables (i.e. psychological distress, quality of life (only for patient), caregiver appraisal (only for partner), relationship quality and spirituality), with treatment as fixed factor, baseline measurement as covariate and a random intercept based on MBSR group. This procedure will use all observed data in our analyses. In addition, Cohen’s *d* effect size [74] will be reported based on the difference between the group means on baseline and follow-up scores, divided by the pooled standard deviation at baseline and follow-up.

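### The cost-effectiveness procedure states no adjustment of incremental QALYs for baseline quality of life, which gives up precision that the collected data could supply

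*Protocol article*

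**What the plan says.** The Cost effectiveness section (protocol article, Secondary analyses) says that the two quality-of-life questionnaires "will be used to calculate Quality of Adjusted Life Years (QALYs) for each individual". Costs and QALYs are then combined into an ICER. Uncertainty is handled as follows: "To estimate confidence intervals for the mean of the ICER a non-parametric bootstrapping method will be used, performing 1000 replications of the original data". An acceptability curve is built on top. No regression or covariate is named at any step.

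The Primary analyses section specifies linear mixed models "with treatment as fixed factor, baseline measurement as covariate and a random intercept based on MBSR group". The outcomes they cover are listed as psychological distress, quality of life, caregiver appraisal, relationship quality and spirituality. QALYs and costs are not on the list.

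Table 1 shows the QLQ-C30 and QLQ-LC13 given to patients at all three time points: "T0 = Baseline measurement; T1 = Post-intervention measurement; T2= 3-month follow-up measurement". The Baseline section places the baseline questionnaires before randomization. The Randomization section stratifies by setting and minimizes on disease stage, HADS category, concurrent treatment and mode of participation; quality of life is not a factor.

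**The concern.** The same questionnaires are analysed with baseline adjustment as a clinical outcome and, as far as the article states, without it once converted to QALYs. If the QALY is an area under the quality-of-life curve, the T0 value is one of its components and is also correlated with T1 and T2. A chance difference between arms at T0 is then counted in the QALY difference. Even if T0 is left out of the QALY, its correlation with follow-up leaves explainable variance unused.

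The QALY difference is the denominator of the ICER and feeds the acceptability curve, so its uncertainty would be wider than the data require. The economic result could also differ from the baseline-adjusted quality-of-life result in the same patients simply because the two analyses treat baseline differently.

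**Working it through.** **The plan's own figure.** The article gives no precision figure for the economic analysis. Its HADS sample size reproduces and supplies the only correlations available:
- Clustering factor: 1 + (7 − 1) × 0.01 = 1.06.
- Factor for repeated measures and baseline: (1 + 0.8)/2 − 0.5² = 0.65.
- Per arm: 64 × 1.06 × 0.65 = 44.1, so 44; total 88; with 20% drop-out, 88/0.8 = 110.

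For the HADS, then, the plan already counts on baseline adjustment.

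**Assumptions for the QALY (none is stated in the article).**
- The QALY is a trapezoid area under the curve over T0, T1 and T2.
- T1 is at 2 months and T2 at 5 months, inferred from an 8-week course plus three months of follow-up.
- Variance is equal (set to 1) at each time, and there are no deaths.
- The correlation of baseline with each follow-up is ρ₀ = 0.5 and between follow-ups ρ = 0.8, both borrowed from the HADS.
- 44 patients per arm are analysed.

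**Step 1: weights.** As shares of the 5 months: T0 = (2/2)/5 = 0.2; T1 = (5/2)/5 = 0.5; T2 = (3/2)/5 = 0.3.

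**Step 2: variance without adjustment.**
0.2² + 0.5² + 0.3² + 2(0.2·0.5·0.5 + 0.2·0.3·0.5 + 0.5·0.3·0.8) = 0.38 + 0.40 = 0.78.

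**Step 3: covariance with T0.**
0.2 + 0.5·0.5 + 0.3·0.5 = 0.60.

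**Step 4: variance after adjustment.**
0.78 − 0.60² = 0.42. Reduction: 0.36/0.78 = 46%. SE ratio: √(0.42/0.78) = 0.73, so the SE is 27% smaller.

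**Step 5: sensitivity to the correlation (ρ = 0.8 throughout).**

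| ρ₀ | Variance, unadjusted | Variance, adjusted | Variance cut | SE cut |
|---|---|---|---|---|
| 0.3 | 0.716 | 0.522 | 27% | 15% |
| 0.5 | 0.780 | 0.420 | 46% | 27% |
| 0.7 | 0.844 | 0.266 | 68% | 44% |

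Placing T1 and T2 at 3 and 6 months, with ρ₀ = 0.5, gives a variance cut of 51% and an SE cut of 30%.

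**Step 6: T0 not part of the QALY.** Averaging the two follow-ups, as in the plan's own factor, gives a variance of (1 + 0.8)/2 = 0.90 unadjusted and 0.65 adjusted: 28% less variance, 15% less SE.

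**Step 7: chance imbalance.** One SE of baseline difference under simple randomization is √(2/44) = 0.213 SD. It moves the QALY difference by 0.60 × 0.213 = 0.128 in units of the quality-of-life SD. Squared, 0.128² = 0.0164 = 0.36 × 2/44, which is exactly the variance removed in Step 4. The shift and the precision loss are one quantity, not two harms.

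**Step 8: from QALY to net benefit.** If QALYs make up half of the net-benefit variance and costs are unrelated to baseline quality of life (both assumptions), the variance cut is 0.5 × 0.46 = 23% and the SE cut is 1 − √0.77 = 12%.

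**The case against.** The strongest reply is that the point is read from silence. The section does not call the QALYs unadjusted, a non-parametric bootstrap is fully compatible with a regression refitted in each replicate, and a condensed article may leave that detail to a fuller plan. Part of this stands: one cannot say that the plan rules adjustment out. But the article describes the procedure down to the number of replications, and its list of baseline-adjusted outcomes omits QALYs and costs. What is written therefore leads to an unadjusted difference.

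Other objections stand and limit the size:
- The correlations belong to the HADS, and no QALY formula is given.
- The Background reports that 60 to 70% of patients die within a year of diagnosis. Deaths add QALY variance that baseline quality of life may explain poorly, and the ranges above do not cover this.
- Minimization on stage, HADS category and treatment may balance quality of life indirectly, so 0.213 SD may overstate the typical imbalance.
- The study is sized on the HADS, and the economic evaluation is secondary.

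A reader might infer that the ICER is biased. The documents do not support that. Allocation is randomized, so baseline imbalance is chance, and the bootstrap interval already includes that variation. A reader might also infer that nearly half the precision of the ICER is lost. That does not follow: 46% is variance, concerns only the QALY component, and rests on borrowed inputs.

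**Conclusion.** The point holds as a low-severity, nearly free improvement. The economic procedure states no adjustment of incremental QALYs for T0 quality of life, although the covariate is collected and is used for quality of life as a clinical outcome. The consequence is an avoidably imprecise QALY difference that chance imbalance can shift, not a systematic error.

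Adjustment reduced the variance in every scenario examined. The central figure (46% in variance, 27% in SE) is conditional on the assumed trapezoid QALY, the visit times, the absence of deaths and the HADS correlations. The range is 27% to 68% in variance for baseline correlations of 0.3 to 0.7, and 28% if T0 lies outside the QALY. The gain for the ICER or net benefit is smaller because costs add variance, and deaths could reduce it further.

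**What to change.** In the Cost effectiveness section, state that the incremental QALY is estimated by regressing each patient's QALY on treatment and the T0 quality-of-life (utility) value. Refit that regression in each of the 1000 bootstrap replicates, resampling each patient's costs and QALYs together. Build the ICER and the acceptability curve from the adjusted differences, and report the unadjusted result as a sensitivity analysis. Stating this before analysis also removes a later choice between the two.

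The cost is a short addition to the text and one extra regression per replicate. No new data are needed. Any missing T0 value would have to be imputed, which should be rare because baseline questionnaires precede randomization.

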### Aims

The aim of the Mindfulness for Lung Oncology Nijmegen (MILON) study is to examine the effectiveness of MBSR compared to TAU in reducing psychological distress in patients with lung cancer and their partners. We hypothesize that patients in the MBSR group will report a lower level of psychological distress (i.e. anxiety and depressive symptoms), higher levels of quality of life, quality of relationship and spirituality than those in the TAU group. Medical and societal costs will be lower in the MBSR versus TAU group. We expect partners in the MBSR group to report a lower level of psychological distress and higher levels of caregiver appraisal, relationship quality and spirituality than their counterparts in the TAU group. With regard to the working mechanisms of the MBSR programme, we will examine changes in mindfulness skills, self-compassion, rumination, intrusion, avoidance and adherence to MBSR.

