#### Costs (only for patients)

The cost-effectiveness evaluation is carried out from a societal perspective, considering direct as well as indirect health costs. Data on costs are collected prospectively using a diary in which participants register a) health care utilization: the type of care and its duration, and b) cancer-related absence from work. Unit cost estimates are derived from the national manual for cost prices in the health care sector [59]. Costs of reduced ability to work are estimated using the friction costs method, which results in a more realistic estimate than the human capital approach [60]. Treatment costs of MBSR are calculated using activity-based-costing methods, thus measuring actual resources (time of therapist, time of patients, facilities) used. All unit cost prices are adjusted to 2013 prices. Unit cost estimates are combined with resource utilization data to obtain a net cost per patient over the entire follow-up period.

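### Mean savings are to be estimated only under dominance and per year from about five months of cost data, and the interval for the mean ICER is unstable if the QALY difference is near zero

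*Protocol article*

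**What the plan says.** The Aims section of the protocol article states a directional cost hypothesis: "Medical and societal costs will be lower in the MBSR versus TAU group". Under Costs (only for patients), diary data and unit prices are combined "to obtain a net cost per patient over the entire follow-up period", with no condition attached.

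The Cost effectiveness subsection plans four things:

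- an ICER from costs and QALYs, without condition;
- uncertainty for it: "To estimate confidence intervals for the mean of the ICER a non-parametric bootstrapping method will be used, performing 1000 replications of the original data";
- an acceptability curve, also without condition: "a cost-acceptability curve will be constructed";
- a savings estimate that depends on the result: "In case of dominance, a full cost analysis will be conducted to estimate the mean savings per patient per year".

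Table 1 has patients keep the cost diary monthly during the study period. The Intervention section gives 8 weekly sessions, and the last assessment is the three-month follow-up.

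**The concern.** There are two separate problems.

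**The savings figure.** Lower cost is a stated hypothesis, yet the one analysis named as giving a mean saving runs only once the data already favour MBSR on both cost and effect. An estimate reported only in that event is biased towards savings when the truth is near zero. It is then to be expressed per year, although no patient's costs are recorded for a year under the described schedule.

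**The interval for the mean ICER.** A ratio whose denominator can be close to zero has no stable mean. When bootstrap QALY differences fall on both sides of zero, the ratio changes sign, and a negative value can mean either that MBSR dominates or that it is dominated. An interval over such ratios mixes opposite conclusions.

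At stake are two figures that readers are apt to quote: an annual saving that was not observed, and an interval for the ICER that cannot be interpreted.

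**Working it through.** **Plan's own figure.** The cost section gives no result to recompute. The number per arm used below comes from the Sample size section and reproduces: (1 + 6 × 0.01) = 1.06; (1 + 0.8)/2 − 0.5² = 0.65; 64 × 1.06 × 0.65 = 44.1, so 44 per arm, 88 in total, and 88/0.8 = 110.

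**Observation period.** I read the three-month follow-up as three months after the post-intervention assessment.

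- Baseline at the start of the course: 56 + 91.3 = 147.3 days = 4.8 months; 365.25/147.3 = 2.48.
- Baseline two weeks earlier (assumed): 70 + 91.3 = 161.3 days = 5.3 months; 365.25/161.3 = 2.26.

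Simple scaling therefore multiplies the observed saving by 2.3 to 2.5. It would also count the one-off course cost 2.3 to 2.5 times, and that part works against savings.

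**Selection.** The documents give no SDs, so these are assumptions: cost SD 5,000 or 10,000 currency units, QALY SD 0.10, correlation −0.2 between the cost and QALY differences, 44 per arm. Dominance means a point estimate with lower cost and higher QALYs. There were 100,000 simulated trials per row. Each cell shows SD 5,000 / SD 10,000.

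| True saving | True QALY gain | Trials with dominance | Mean saving in those trials, observed period |
|---|---|---|---|
| 0 | 0 | 28% / 28% | 900 / 1,820 |
| 1,000 | 0.02 | 70% / 58% | 1,370 / 2,170 |
| 2,000 | 0.02 | 81% / 70% | 2,130 / 2,720 |
| 4,000 | 0.03 | 92% / 90% | 4,030 / 4,210 |
| −1,000 (MBSR dearer) | 0.02 | 16% / 28% | 580 / 1,400 |

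In the first row, scaling by 2.48 gives about 2,200 / 4,500 per year when the truth is zero. With a true saving of 4,000 the bias nearly vanishes.

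**Size of the QALY difference.** The horizon is 147.3/365.25 = 0.40 year. A utility gain of 0.05 held throughout is 0.05 × 0.40 = 0.02 QALY. A gain of 0.05 QALY would need 0.05/0.40 = about 0.12 utility throughout.

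**Stability of the ratio.** For each assumed QALY gain, one simulated data set (44 per arm, QALY SD 0.08 assumed) was bootstrapped with 1000 replicates under 10 random seeds. The cost data were the same throughout, with MBSR dearer by about 120.

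| QALY gain | Point ICER | Mean of replicate ICERs, range over 10 seeds | Replicates with QALY difference ≤ 0 | 2.5 and 97.5 percentiles, one seed |
|---|---|---|---|---|
| 0.01 | 12,000 | −239,000 to 2,790,000 | about 25% | −985,000 to 1,124,000 |
| 0.02 | 6,000 | −174,000 to 73,000 | about 10% | −463,000 to 647,000 |
| 0.05 | 2,400 | 1,600 to 10,000 | almost none | −65,000 to 85,000 |

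At 0.01 and 0.02 the mean depends on the seed. The tails of the percentile interval are driven by replicates with a QALY difference close to zero, on either side.

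**The case against.** A reader might infer that the trial's whole cost conclusion is selected, extrapolated and unstable. The documents do not support that. The costs section states: "Unit cost estimates are combined with resource utilization data to obtain a net cost per patient over the entire follow-up period". The ICER uses the incremental cost whichever way it falls, and dominance cannot be judged until that difference has been computed. The savings figure is a contingent last step in a secondary analysis. This objection stands, and it limits the point to that figure and to the ICER interval.

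The acceptability curve is a sound answer to the ratio problem, since each point on it is the share of replicates with positive net benefit. At a threshold of zero it even shows the share with lower cost. That also stands. But the curve does not give the size of the cost difference, and it does not repair an interval that is planned separately.

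The reference to the mean of the ICER may be loose wording, and the article does not say that replicate ratios are averaged. This is fair. A percentile interval of replicate ratios nevertheless mixes quadrants in the same way once QALY differences cross zero.

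The article does not describe the full cost analysis or how annual figures are formed, and a condensed article may leave the method to the full protocol. So the absence of a method is not the complaint. The article does fix a yearly target that its own data collection does not reach.

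A reader might also turn the first-year mortality in the Background section into a multiplier for overstated annual costs. That mortality runs from diagnosis, whereas the trial admits patients already treated, including those at a curative stage, and costs observed during follow-up already reflect deaths in that period. No such multiplier is supported.

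**Conclusion.** The point holds in a limited form. Two facts follow from the article alone: the mean saving is conditional on dominance, and its yearly unit exceeds the observed period by a factor of about 2.3 to 2.5 (taking baseline as 0 to 2 weeks before the course).

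The bias towards savings holds if dominance, which the article does not define, is judged on point estimates. Its size depends on the assumed SDs and effects: marked when the true cost difference is small, negligible when the saving is large. The instability of the ICER interval likewise depends on an assumed QALY SD and gain. It is serious at 0.01 to 0.02 QALY, the range that a 0.4-year horizon makes likely, and much reduced at 0.05.

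No analysis described in the article gives the hypothesised cost difference an interval in both directions: the mixed-model outcome list under Primary analyses omits costs, and the bootstrap interval is for the ICER. The unconditional cost-effectiveness results, the primary outcome and the sample size are unaffected. This is a cheap improvement to a secondary analysis.

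**What to change.** 1. Report the between-arm mean cost difference with a bootstrap interval over the observed follow-up, whatever its sign and whatever the ICER quadrant. This tests the cost hypothesis in the Aims directly.
2. Delete the per-year expression. Alternatively, label it an extrapolation, state its assumptions, and do not annualise the one-off course cost.
3. Replace the interval for the mean ICER with incremental net monetary benefit and its interval over a range of thresholds. Keep the acceptability curve, and report the point ICER where it can be interpreted.

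The cost is a change of analysis wording, with no added patients or data. The annual savings figure is lost or qualified.
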